#### Recruitment

Recruitment of participants will utilise multiple pathways, including:Contacting PWD identified from searches on NHS research, NHS clinic, and voluntary sector databases.Opportunistic recruitment of patients using NHS memory assessment service clinics, NHS older people mental health services, NHS outpatient clinics, voluntary sector memory advisors, and GPs.Recruitment via the Join Dementia Research website, endorsed by the Health Research Authority, to facilitate patient recruitment into dementia studies (http://jdr-delivery.nihr.ac.uk/).Recruitment via potential participants’ direct responses to study promotion including leaflets/posters in dementia cafés, support groups, general practices, chemists, pharmacies, day-care centres, newspapers, radio, social media, and informal newsletters.

All potential participants will be asked if they are willing for their contact details to be provided to a member of the TACIT research team.

A member of the TACIT research team will contact potential participants to arrange an initial visit, typically at the potential participant’s home. The researcher will wait a minimum of 48 h before contacting potential participants to ensure they have had sufficient time to consider the information in the Participant Information Sheet. Both PWD and carer must be present at the initial visit and both must provide written informed consent. Researchers will use process consent with PWD, which is established in the evidence base [43–45], in that consent will not be assumed for the duration of the visit or for the project after provision of initial informed consent. Informed consent will be re-confirmed verbally throughout the project.

After consent has been obtained, the researcher will administer the M-ACE to the PWD to confirm that they meet the entry criterion in relation to dementia severity. As version A is used in routine care, version B will be used at baseline and version C at follow-up (to reduce potential bias due to practice effects). Participants recruited from outside NHS / GP services will be required to sign a consent form to enable the research team to verify the PWD’s dementia diagnosis (type and when diagnosed) from their memory assessment service or provide written evidence of their diagnosis.

### Assignment of interventions

In this trial we will aim to achieve equal balance of recruitment of participants between treatment conditions according to the following key prognostic variables: dementia type (due to eligibility criteria, this will be relatively homogenous in this study), age, fall history, and dementia severity. These are important variables because impairment in postural stability will be elevated among those who are older, have fallen in the past 12 months, and present with more severe dementia symptoms [19, 20]. Given that these key prognostic variables are positively correlated [19, 20], only one variable - fall history at baseline: has / has not fallen within the previous 12 months – was selected for a parsimonious and achievable strategy for balancing prognostic factors. The method of allocation needed to accommodate a trial design that allowed for variability in Tai Chi class size according to a dynamic recruitment process. Therefore, to ensure balance within each of the three treatment sites (and across the entire trial), minimisation will be used within each site to achieve a balance in fall history.

For each of the 11–15 classes, once a minimum of 4 dyads in total have been recruited, the dyads will be randomised to the intervention or control group. Random allocation will be achieved using a centralised automatic web-based randomisation system designed and maintained by the UKCRC-registered Peninsula Clinical Trials Unit (CTU). Once a minimum batch of 4 dyads has been recruited within a treatment site, the first dyad will be allocated using simple randomisation and the remaining dyads allocated using minimisation. Afterward, any further dyads recruited into the study before the fifth class has taken place will be randomised individually by minimisation and join the class if so allocated.

#### Outcome assessor blinding

Baseline measures will be recorded at the PWD’s home before randomisation is performed. After the home visit, dyads will be informed in writing of their treatment arm allocation by staff at the CTU. Given the nature of the intervention, it will not be possible to keep PWD, carers or Tai Chi instructors blind to treatment arm allocation. The researcher who collects baseline data will be kept blind to treatment arm and, in particular, when they conduct the six-month post-baseline follow-up home visit. Participants will be asked at the time of arranging the follow-up visit and at the beginning of the follow-up home visit not to disclose their treatment condition, and to conceal any evidence of participating in class or home-based Tai Chi. After data collection is completed for each follow-up visit, the researcher will make a note of their guess of the treatment arm for the dyad and if dyads accidentally disclose their treatment condition.

#### Blinding of data analysis and interpretation

Copies of the completed case report forms (CRFs), labelled with a unique trial number for each dyad member, will be sent to the CTU for double data entry into a web-based trial database designed and maintained by the CTU. The data will be exported for the statistician with treatment condition unblinded since information on class cohort is required for the analysis. Once the analysis is complete, the results will be revealed to the rest of the research team with trial arm identity concealed. After the results have been discussed and interpreted, the results will be unblinded for the research team to complete their interpretation and to begin dissemination of the findings.

### Data collection, management, and analysis

The CTU will seek clarification on any data queries with the researcher that will prompt the researcher to seek clarification from the PWD at the next scheduled telephone call. All data will be stored according to the UK Data Protection Act and the General Data Protection Regulation. Anonymised and identifiable study data will be stored separately to prevent the identification of participants from research records, in locked filing cabinets within a locked office. All digital records will also be securely stored on backed up university servers with restricted access. Data held on BU laptops will also be protected through encryption and network authentication and transferred to the secure trial folder as soon as possible. Data will be double-entered by CTU staff on to a password-protected SQL Server database and encrypted using Secure Sockets Layer.

#### Statistical methods

A detailed statistical analysis plan will be finalised separately before follow-up data collection is complete. Participants will be analysed in the group they are randomised to, and (with the consent of participants) we will attempt to collect complete data on everyone and use those data in the analyses. Descriptive statistics will be presented for all baseline outcome data for each trial arm separately. Descriptive statistics will be presented on the following for the PWD and their carer: gender, age, relationship status, current living arrangements, education level, ethnicity, previous experience of Tai Chi and treatment site. Additional descriptive statistics will be presented in relation to PWD: type of dementia, time since diagnosis, other long term conditions, existing injuries, use of a walking aid, number of medications currently taken, falls history (in past 12 months and past month), and current level of physical activity (moderate and vigorous).

Mean TUG scores at 6 months, the primary outcome, will be compared between the two trial arms using a mixed (multi-level) model approach to take into account clustering resulting from the group-based nature of the Tai Chi intervention. Baseline TUG, treatment site, and falls history in the past 12 months (Y/N) will also be included in the model. We will assume that the missing data mechanism is “Missing at Random” (MAR). No imputation methods will be used for the main analysis but will be explored in additional analyses. The method of analysis will be similar for other secondary outcomes for the PWD and carer. In addition, falls count data and the proportion of participants who fell will be analysed using negative binomial and logistic models respectively, taking into account falls history and treatment site. We will also conduct a per protocol analysis that will exclude participants from the Tai Chi group if they received fewer than 50 h (the intended minimum dose of the intervention).

One subgroup analysis is pre-planned for the primary outcome variable (TUG). Fall history at baseline (had a fall or not in the past 12 months), which is also the variable used for minimization in addition to treatment condition, will be entered as an interaction term in a statistical model (intervention effect x effect modifier). Departures from the proposed analysis, for example due to poor recruitment, will be explained and justified in the main trial paper. Feasibility objectives will be addressed by estimating recruitment and attrition rates (with 95% confidence intervals) and falls data parameters (falls rate, proportion of fallers, and completeness of falls data) for a future sample size calculation. In addition, we will compare the frequency of falls reported by each of the individual methods of data collection and their combination to determine if the increased resource in collecting falls data weekly provides more accurate data.

Descriptive data from the structured exit interviews will be presented on hypothetical willingness to pay for the intervention and perceived changes to health (PWD and carer). Data on number of Tai Chi classes attended and adherence to home practice will be presented. To assess adherence to the intervention in the Tai Chi arm we will calculate: adherence to classes (i.e. x attended out of y possible) and adherence to home exercise (i.e. x minutes exercise out of y recommended). The following data will not be reported in the main trial outcome paper but will be included in further secondary analyses in relation to visual spatial cognitive functioning (statue task); comparison of the different methods of data collection on incidence of falls; qualitative data; and uptake and adherence to the intervention (whether the PWD or carer had done Tai Chi before, mean (SD) intention and perceived behavioural control to do Tai Chi, and intervention group responses to the questionnaire delivered half way through the intervention).

Given the short-term (6-month) follow-up, low-risk intervention being tested, and no planned interim analyses, there will be no data monitoring committee for the trial. The trial will only be stopped early if the intervention is considered to be directly causing undue harm to patients as independently considered by the trial steering committee and/or NHS Research Ethics Committee.

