#### Sample size

A formal sample size calculation was undertaken based on detecting a difference in mean timed up and go (TUG) test scores between the intervention and control arms of the study. We found no studies looking at minimum clinically important difference, but did find two studies that had estimated smallest detectable change (i.e. the smallest change that we can be reasonably sure is not measurement error). The two values were 4.09 [41] and 5.88 [37], and we used a conservative value of 4. To find an estimate of standard deviation (SD) for TUG, we found several relevant papers but the values were sensitive to the mix of age and severity of dementia, with one study that seemed to most closely match our population and be based on a reasonable sample size (*n* = 58) [37]. SDs from two different time points were presented (9.74 and 9.01) and we used the average of these (9.38) [37]. In our analysis we will enter baseline TUG as a covariate and assume a correlation of 0.7; test-retest reliability of TUG is excellent [37, 42] but we acknowledge the duration between time points in our study will be longer than prior studies and so we have used a more modest correlation.

Therefore, using a mean difference in TUG of 4, an SD of 9.38, a correlation of 0.7 and a 2-sided 5% significance level, the study will have 90% power when the sample size is 120 (60 per group). Allowing for up to 20% withdrawal / non-completion of outcome measures, we will recruit 150 dyads into the trial (75 per group). These calculations were conducted using nQuery Advisor 7.0. The intervention partly takes place in classes, and there is a possibility of clustering effects. However for the purposes of the sample size calculation we have assumed that these will be negligible, because (a) much of the intervention occurs outside the class environment, and (b) interaction between PWD is not a specific purpose of the intervention’s effect on the primary outcome (only to enhance adherence to the intervention). Clustering effects will be considered in the statistical analysis.

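### The primary TUG model leaves out age and dementia severity, which the protocol itself calls prognostic and already collects; adding them is a small, nearly free improvement to a valid analysis

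*Protocol article*

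**What the plan says.** Under Statistical methods, the protocol article compares mean 6-month TUG between arms in a multi-level model that allows for clustering by Tai Chi class. On covariates it says: "Baseline TUG, treatment site, and falls history in the past 12 months (Y/N) will also be included in the model". It assumes that data are missing at random and adds: "No imputation methods will be used for the main analysis but will be explored in additional analyses". Similar models are planned for the secondary outcomes, and a detailed statistical analysis plan is to follow.

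Under Assignment of interventions, the article aims to balance the arms on "key prognostic variables: dementia type (due to eligibility criteria, this will be relatively homogenous in this study), age, fall history, and dementia severity". It explains that "impairment in postural stability will be elevated among those who are older, have fallen in the past 12 months, and present with more severe dementia". Because these variables are positively correlated, only fall history is used for minimisation, within site.

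Under Sample size, it reports that published TUG standard deviations varied with the age and dementia severity of the sample. The calculation itself adjusts for baseline TUG only.

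Both omitted variables are available. M-ACE is administered at the initial visit, and age is among the baseline descriptors for the person with dementia and for the carer.

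**The concern.** The article gives its own reasons to expect age and severity to predict the primary outcome, then uses neither in allocation nor in the model. The parsimony argument concerns the minimisation scheme. No reason is given for leaving the two variables out of the model, where they cost little.

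Three things are at stake:

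- **Precision.** Prognostic information already collected is not used.
- **Chance imbalance.** Age and severity are not minimised on, so a chance difference between arms is corrected only as far as baseline TUG, site and fall history carry it.
- **Missing data.** TUG has one follow-up time. Without imputation, a participant with no 6-month TUG contributes nothing to the main estimate, so missing at random has to hold given arm, class, baseline TUG, site and fall history alone. The design makes arm-specific dropout conceivable: Tai Chi dyads take on weekly classes and daily carer-supported practice, while controls do not and are offered no waiting list.

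**Working it through.** **Inputs from the article (Sample size).** Difference d = 4 s, SD 9.38 s, correlation with baseline 0.7, two-sided 5% level, 60 analysed per group, 90% power. The inflation is described as "Allowing for up to 20% withdrawal / non-completion of outcome measures", giving 150 recruited.

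**Reproducing the plan's figure.**

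- Residual SD after baseline: s = 9.38 × √(1 − 0.7²) = 6.70 s.
- Normal approximation: n = 2 × 6.70² × (1.960 + 1.282)² / 4², which rounds up to 59 per group.
- Power at 60 per group: SE = 6.70 × √(2/60) = 1.223 s, so power = Φ(4/1.223 − 1.96) = 90.5%.
- Noncentral t: 90.04% at 60 per group and 89.5% at 59, so 60 per group is right.
- 120 / (1 − 0.20) = 150.

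The stated power does not depend on age or severity being in the model.

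**Precision.** The documents do not say how much residual variance age and M-ACE would explain. I assume a share R² of 2%, 5% or 10%. The residual SD becomes 6.70 × √(1 − R²).

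| Assumed R² | SE (s) | Power at 60 per group | n per group for 90% |
|---|---|---|---|
| 0 | 1.223 | 90.5% | 59 |
| 2% | 1.211 | 91.1% | 58 |
| 5% | 1.192 | 91.9% | 56 |
| 10% | 1.160 | 93.2% | 54 |

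(Normal approximation throughout.)

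**Chance imbalance.** If the part of age and severity not captured by the existing covariates differs between arms by 1.96 standard errors, the estimate shifts by 6.70 × √R² × √(2/60) × 1.96 = 2.40 × √R²:

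- R² = 2%: 0.34 s (8% of 4 s)
- R² = 5%: 0.54 s (13%)
- R² = 10%: 0.76 s (19%)

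These are unlucky draws, not expected values. Across repeated randomisations the average shift is zero.

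**Missing data.** A simulation of 2 million records per scenario used residual SD 6.70 s, a true effect of −4 s and 20% missing in each arm. Missingness depended on a standard-normal age/severity index that was left out of the model. The index stands for what remains after conditioning on baseline TUG, and class clustering is ignored. The log odds ratios per SD of the index are assumed. With about 800,000 observed per arm, the Monte Carlo error is about 6.70 × √(2/800,000) = 0.01 s.

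| Dependence of missingness on the index | Bias, R² = 2% | R² = 5% | R² = 10% |
|---|---|---|---|
| Same in both arms (0.7) | 0.01 s | 0.01 s | −0.01 s |
| Tai Chi arm only (0.7) | −0.11 s | −0.19 s | −0.27 s |
| Tai Chi arm only (1.1) | −0.17 s | −0.27 s | −0.41 s |
| Opposite in the two arms (±0.7) | −0.25 s | −0.40 s | −0.54 s |

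Negative values overstate the benefit of Tai Chi; reversing the roles of the arms reverses the sign. With the index in the model, bias was within 0.02 s of zero in every scenario.

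**The case against.** The strongest reply is that nothing is stated wrongly. Baseline outcome, site and the minimisation factor form a standard and valid covariate set that matches both the allocation and the sample size. Calling a variable prognostic does not oblige the model to include it, and randomisation keeps inference valid despite chance imbalance. The article says the prognostic variables are correlated with one another, so fall history carries part of what age and severity would add, and baseline TUG plausibly carries more. All of this stands. It limits the gain but does not reduce it to zero: fall history is a yes/no item, and baseline TUG at the assumed correlation leaves 1 − 0.49 = 51% of the variance unexplained.

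Imputation is also not ruled out. It is kept for additional analyses, where age and M-ACE could enter, and the variable list belongs in an analysis plan that is not shown. This softens the missing-data point, though those analyses do not alter the primary estimate.

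Two stronger readings are tempting. A reader might infer that the primary analysis is biased or underpowered as written. The documents do not support that: the power reproduces, and the bias is about zero unless age or severity drives missingness differently in the two arms, for which they give no evidence. A reader might also infer that someone seen at 6 months but unable to do the TUG is treated as an ordinary missing value, hiding a poor outcome. The article does not say how such a person is handled. Its allowance for non-completion serves only to inflate the sample size, and such a rule is commonly left to the analysis plan.

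**Conclusion.** The point holds as a modest improvement, not as an error. The primary model is valid and the sample size stands. What the article fixes without a reason is a covariate set that omits two baseline variables it describes as prognostic and already collects, in an analysis that rests on complete cases.

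The size is small and depends on assumed inputs. Power gains about 1 to 3 percentage points if age and M-ACE explain 2–10% of the residual variance. Bias of about 0–0.5 s (up to roughly 13% of the 4 s target) is avoided only if missingness depends on them differently by arm. Protection against an unlucky imbalance is of similar order.

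**What to change.** Before follow-up data collection is complete, pre-specify the following:

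- **Primary model:** add the baseline age and baseline M-ACE of the person with dementia as continuous covariates, alongside baseline TUG, site and fall history.
- **Secondary models for the person with dementia:** the same two covariates. Where M-ACE is itself the outcome, its baseline value would be in the model already under a similar analysis, so only age is new.
- **Carer outcomes:** the carer's own age.
- **Additional imputation analyses:** include age and M-ACE among the imputation variables.

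The cost is a change of wording and two degrees of freedom in the primary model. No new data are needed and the sample size does not change. Settling this early matters because the statistician will work with unblinded data, and covariates added after that would be open to challenge.

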This protocol describes a randomised controlled trial (RCT) that aims to test the effectiveness of Tai Chi to improve postural balance among community-dwelling PWD and to assess the feasibility of conducting a definitive trial to reduce falls. We hypothesise that Tai Chi will help prevent falls by improving dynamic balance. Dynamic balance is highly predictive of rate of falls [18–20], and so it will be used as a surrogate outcome in this trial. This research programme is the first in the UK to test the effectiveness of Tai Chi to improve balance among PWD (current study) and the first in the world to use Tai Chi in a randomised controlled trial to prevent falls among PWD (future study). The trial is registered on ClinicalTrials.gov (ID no: NCT02864056, first posted August 11th, 2016) and this paper is a summary of the protocol version 4.3, dated 23/05/2018. To test if the new intervention can provide patient benefit in addition to usual care, no alternative intervention or waiting list control group will be offered.

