#### Outcomes

The majority of measures will be taken at baseline and six months post-baseline (see Table 3). Weekly telephone calls with PWD for data collection will also serve as weekly contact to encourage retention. If one member of a dyad wishes to withdraw from the study, or is advised to withdraw by their general practitioner, they will be asked whether they are willing for data gathered up to the point of withdrawal to be retained for intention-to-treat analysis.

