**Primary outcome**				
Difference in score from the person with dementia between the two arms at six months post-baseline:				
Timed Up and Go (TUG) test [64]	Dynamic balance	Continuous measure of time (in seconds) to complete the task. A cut-off point will not be used because there is no value that can be recommended from existing evidence [48, 49].	In addition to using a stopwatch, performance on the TUG will be measured using a Balance Sensor (THETAmetrix) that contains an accelerometer to digitally record biomechanical movement, and is a small, inexpensive device that is wireless and corrects for tilt dynamically. The data on the device will be downloaded immediately after each test and stored on the researcher’s laptop / tablet and labelled using the participant’s unique ID number.	The TUG is quick and simple to administer in the community [49] and has been recommended for screening for falls risk [50] and assessing gait and balance for preventing falls [51]. While no particular measure of dynamic balance has been recommended in the literature, systematic reviews have identified that the TUG has excellent reliability [42], a strong correlation with falls in retrospective studies [47], is more effective at ruling in falls (0.74 specificity) among individuals classified at high risk of falls [52], and is more suitable with older people who are relatively less healthy and have lower functioning [48]. Devices such as the balance sensor have been shown to produce reliable and valid data for the TUG and its subcomponents [53, 54].

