Falls measurements will be collected prospectively from baseline until six months post-baseline. These include the number of falls by PWD (count data), the proportion of PWD who have fallen (binary outcome measure), and number of injurious falls (count data). The collection of falls data is in accordance with recommendations made by the Prevention of Falls Network Europe (ProFaNE) [38]. In our trial, the definition of a fall is, “an unexpected event in which the participants come to rest on the ground, floor or lower level” [38]. Falls will be recorded by dyads daily using prospective monthly calendars and returned on a monthly basis by post for data entry. Where falls are reported by dyads or calendars are not returned, a researcher will conduct a telephone interview to collect further information about the fall/clarify missing data. Telephone calls will be conducted weekly with the PWD as recommended for falls data collection with PWD [39]. In addition, to ascertain the accuracy of different recall periods, telephone calls about fall incidents by the PWD will be made monthly with the PWD and every 3 months with the carer. Fall injury will be recorded by telephone interview when recording falls as described above, using an existing set of definitions for severity of injury ([11, 40], p.).

Within the intervention group only, data will be collected half-way through the intervention on a 5-item questionnaire to ask about the importance of features of the intervention such as enjoyment of the classes and confidence in being able to continue to do the home practice. At the end of the final home visit, all dyads will be asked to complete a brief structured exit interview that asks about their hypothetical willingness to pay for the Tai Chi intervention should it be offered in the future as part of routine NHS care. The researcher will also ask participants if there have been any significant changes during the trial to their medical status (e.g. medication usage or elective surgery), which may influence performance on the primary outcome.

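### The negative binomial falls models leave out baseline TUG, a prognostic value already collected; this biases nothing but gives up a little precision in the falls rate ratio

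*Protocol article*

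**What the plan says.** All references are to the protocol article; the separate SAP that it announces is not at hand.

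- **Primary model (Statistical methods).** "Baseline TUG, treatment site, and falls history in the past 12 months (Y/N) will also be included in the model".
- **Falls models (same paragraph).** Falls counts and the proportion of fallers are analysed by "negative binomial and logistic models respectively, taking into account falls history and treatment site". Baseline TUG is not mentioned here.
- **Why TUG is the primary outcome.** The Background states: "Dynamic balance is highly predictive of rate of falls". The TUG row of Table 4 cites "a strong correlation with falls in retrospective studies". Neither place gives a coefficient.
- **When the data arise.** Under Outcomes: "The majority of measures will be taken at baseline and six months post-baseline". TUG is among these measures, and the section on assessor blinding puts the baseline visit before randomisation. For falls: "Falls measurements will be collected prospectively from baseline until six months post-baseline".
- **Allocation (Assignment of interventions).** "minimisation will be used within each site to achieve a balance in fall history". Age, dementia severity and dementia type were considered and set aside, with the reason "Given that these key prognostic variables are positively correlated".

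**The concern.** The trial treats balance as a surrogate for falls. If that premise is right, baseline balance should predict who falls during follow-up, and the trial measures it on each person with dementia before allocation. The primary model uses both baseline TUG and falls history, so the authors treat the two as distinct there. The falls models keep only the yes/no history.

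In a count model, differences between people that a baseline covariate could explain go into the dispersion parameter if that covariate is left out, and the confidence interval for the rate ratio widens. Chance imbalance is another view of the same loss. With 60 per arm, the difference between arms in mean baseline TUG has standard deviation √(2/60) = 0.18 SD, so about one trial in 20 has a difference beyond 1.96 × 0.18 ≈ 0.36 SD (slightly less given the balance on falls history). At an assumed rate ratio of 1.5 per SD, that shifts the falls rate ratio by a factor of 1.5^0.36 ≈ 1.16. Adjustment removes this shift.

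At stake is the width of the interval around the trial's estimate of the effect on falls, which is the outcome intended for the later definitive trial.

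**Working it through.** **1. The plan's own figure.** The article states no power or precision for falls. Its only sample size is for TUG: difference 4, SD 9.38, correlation 0.7, two-sided 5%, 90% power.

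- Adjusted SD = 9.38 × √(1 − 0.7²) = 6.70.
- n per arm = 2 × (1.960 + 1.282)² × 6.70² / 4² ≈ 59 by normal approximation. With 60 per arm the power is 90.0% by noncentral t.
- 120 / (1 − 0.20) = 150.

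This reproduces. For its own outcome, baseline TUG is assumed to leave 1 − 0.7² = 51% of the variance. The gain for falls is much smaller.

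**2. Negative binomial model, with and without baseline TUG.** Two sets of simulations were run, both with falls history already in the model and a treatment rate ratio of 0.68 (the pooled across-settings figure for strength and balance training in the Background). All other inputs are assumptions.

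- *Set A:* 150 people, 600 trials per setting; 0.6 falls in six months without falls history; rate ratio 2 for falls history; dispersion k of 0.5 or 1; correlation 0.35 between TUG and the trait behind falls history.
- *Set B:* 120 people, 500 trials per setting; control mean 0.5, 1 or 2 falls in six months; dispersion 1; falls-history rate ratio about 2; moderate correlation of TUG with falls history; site in the model.

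Variance cut = 1 − (SE with TUG / SE without)².

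| Rate ratio per SD of TUG | Set A: SE without → with | Set A: variance cut | Set B: SE cut | Set B: variance cut |
|---|---|---|---|---|
| 1.2 | 0.227 → 0.225 (k = 0.5); 0.256 → 0.254 (k = 1) | 1.8%; 1.6% | 0.4 to 0.7% | 0.8 to 1.4% |
| 1.5 | 0.232 → 0.222; 0.264 → 0.256 | 8.4%; 6.0% | 2.2 to 4.2% | 4.4 to 8.2% |
| 1.8 | 0.238 → 0.217; 0.270 → 0.253 | 16.9%; 12.2% | not run | not run |
| 2.0 | not run | not run | 5.6 to 8.6% | 10.9 to 16.5% |

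Allowing for rounding of the SEs, the cuts are about 1 to 2% at 1.2, 4 to 9% at 1.5, and 11 to 17% at 1.8 to 2.0. In Set B with a ratio of 1.0 (no association) the SE did not change. Power in Set B rose by 1 to 2 percentage points at 1.5 and 3 to 4 points at 2.0.

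**3. The same in participants.** With 120 analysed, a variance cut v is worth 120/(1 − v) − 120 extra people: about 1 at 1%, 5 at 4%, 12 at 9%, 15 at 11% and 25 at 17%.

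**4. Logistic model for fallers (Set B).** Adding baseline TUG raised the SE of the log odds ratio by about 1% at 1.0, 1.2 to 1.4% at 1.2, 2.5 to 2.8% at 1.5 and 5.0 to 5.9% at 2.0. The estimate moved away from zero, for example from −0.35 to −0.38, because the odds ratio is non-collapsible: conditioning on a further prognostic variable changes what is estimated. Power was unchanged within simulation error.

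**The case against.** The model as written is valid and coherent. Falls history is the baseline counterpart of the falls outcome, just as baseline TUG is of follow-up TUG, and history and site are the factors used in allocation. Type I error is not affected. The article itself says that postural stability is more impaired in those who have fallen, so the history variable already carries part of what TUG would add. The retrospective correlation cited in Table 4 concerns past falls, which are in the model. What matters is the association left after falls history, and no section gives it. The short covariate phrase need not be exhaustive, and the SAP may add to it.

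All of this stands. It limits the size and weight of the point but does not remove it: the article names covariates for the falls models, TUG is not among them, and the direction for the count model is clear if TUG has any residual association with falls.

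A reader might infer more than the article supports:

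- *That the falls analysis is wrong or biased.* It is not. Only efficiency is affected.
- *That both falls models lose precision.* The logistic SE rises when TUG is added, so no precision gain can be claimed there.
- *That the feasibility results suffer.* The falls quantities to be carried into a future sample size are the falls rate, the proportion of fallers and data completeness. None depends on the covariates in the treatment-effect model.
- *That the change is free.* It uses one parameter, needs a choice of form for TUG, and would drop anyone without a baseline TUG unless this is handled. The last risk is limited, because the primary model needs that value too.

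**Conclusion.** The point holds for the negative binomial models only, as a minor efficiency improvement. The direction is well supported, but the size is not known. The gain is negligible if TUG predicts falls only weakly once history is known, and reaches the upper end of the range above only if the residual association is as strong as 1.8 to 2.0 per SD. These figures rest on assumed falls rates, dispersion, a falls-history ratio and a TUG-history correlation that the article does not provide. Falls are a secondary outcome with no power claim, so nothing in the trial's main conclusion depends on this.

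**What to change.** In Statistical methods and in the SAP, before follow-up outcomes are examined:

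1. State that the negative binomial model for falls counts includes baseline TUG as a continuous covariate, in addition to falls history and site. Fix its functional form in advance (seconds, or log seconds in view of likely skew).
2. State a simple fill-in for a missing baseline TUG, for example the overall baseline mean ignoring arm, so that nobody is dropped. Say that this is compatible with the rule against imputation in the main analysis because it concerns a baseline covariate and not an outcome.
3. For injurious falls, where events may be sparse, state in advance that the model falls back to history and site if it cannot be fitted.
4. Leave the logistic model for fallers as it is, or add baseline TUG only alongside a standardised marginal estimate, so that the reported effect keeps a clear meaning.

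The cost is a few lines of text and one extra parameter. No new data are needed. Naming the covariate now also avoids any appearance of choosing the adjustment after seeing results.
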